#### Power calculation

An a priori power analysis (G**Power 3.1*) for a two-group, three-time-point repeated-measures ANOVA on the group×time interaction (α=0.05, two-tailed) indicates the following: detecting a moderate interaction effect (Cohen’s f=0.25; ≈ηp²≈0.06) requires N≈34 total (≈17/group) for 80% power. Allowing for~15% attrition over follow-up, we will recruit n=40 (20 per arm) to ensure ≥80% power to detect a moderate effect. The target effect size is justified by prior SCI neuromodulation studies showing moderate-to-large gains in hand/arm outcomes.^75^

##### Project management

*Daily Management:* Project oversight will occur at multiple levels. A weekly 15-min scrum meeting between the clinical and research leads will allow close monitoring of project progress and identification of barriers or facilitators to its smooth implementation. The leads will report to the CIME Programme research coordinators, who meet weekly with the principal investigators to discuss updates, issues or notable changes. The principal investigators will also meet semi-annually (or more frequently if required) with the managers of the SCI units to review project activity, resource use and any emerging concerns. In parallel, the project team will provide weekly updates to the SCI physiatrists to ensure they are informed about participant involvement and can interact rapidly with the research team if needed—particularly important since the intervention occurs early after injury. The research team will also meet weekly with the infection-control officer to confirm adherence to all safety protocols. In the event of a nosocomial or other infection, appropriate personal protective equipment (eg, gloves, masks and gowns) will be used to ensure the safety of both participants and staff.

*Training of research personnel:* To ensure the consistency of training with several therapists and clinicians involved, a structured training process, including multiple training sessions, mentoring and assessment of the fidelity of the intervention, will be implemented to maintain data quality and ensure uniform intervention delivery among all CIME interventionists. The training will include theoretical instructions, a detailed review of each section of the ABT protocol for clinicians and proper placement, parameter setting and assessment of facilitation effects for tSCS technicians. A detailed manual of procedures will be written and used. Regular meetings with all therapists will be held quarterly to discuss any outstanding issues and ensure adherence to intervention protocol. Ongoing supervision and periodic assessment will ensure consistency and fidelity throughout the trial.

##### Safety and adverse events

###### Data Safety and Monitoring Board

A Data Safety and Monitoring Board (DSMB) will be established to oversee participant safety and ensure the scientific and ethical integrity of the study. The DSMB will comprise the head physiatrist of the SCI unit at the research centre, the research coordinators and an independent researcher with expertise in clinical trials. The DSMB will convene every year or on an ad hoc basis if safety concerns arise. Its responsibilities include monitoring participant safety through annual reviews of AEs and unanticipated problems, ensuring the study is conducted ethically and with scientific rigour, and—if necessary—recommending modifications to address any raised issues. Recommendations may be based on evidence of significant adverse effects in the experimental group or on ethical considerations.

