### Secondary objectives

To determine the safety of the intervention (ie, minor and major adverse events (AEs)).To determine changes in sensory and motor function measured by functional clinical assessments.To explore the neuroplastic effects of the ABT+tSCS training programme on:Spinal circuits, assessed via transpinal-evoked potentials (TEPs) using single-pulse tSCS;Corticospinal pathways, assessed via motor-evoked potentials (MEPs) using transcranial magnetic stimulation (TMS);Somatosensory pathways, assessed via somatosensory-evoked potentials (SSEPs) using electroencephalography (EEG).

We hypothesise that ABT+tSCS training will lead to greater improvements than ABT alone in the primary and secondary clinical and neurophysiological measures.

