### Recruitment and consent

Participants will be recruited from the SCI units at the IRGLM from 1 September 2026 to 31 August 2028. Potential eligible participants will be identified by clinicians based on the inclusion and exclusion criteria (presented in table 1) and referred to the study team. Criteria will be reviewed by the research team. Given the haemodynamic instability frequently observed during the acute phase following SCI,^29^ some individuals may be ineligible for enrolment in the CIME trial, either temporarily or permanently. Clearance from the treating medical team will be obtained prior to enrolment.

**Table 1 T1:** Inclusion and exclusion criteria

Inclusion criteria	Exclusion criteria
Traumatic and non-traumatic spinal cord injury	Cardiac pacemaker
Receiving in-patient rehabilitation	Active cancer at the stimulation site or metastatic cancer
Age≥16 years	Unstable lesion or clinical condition (eg, respiratory issues)
American Spinal Injury Association (ASIA) grade A–D	Electrode placement is impossible due to unhealed wound or significant local pain
Neurological level of injury between C5 and T2	Other neurological conditions (eg, stroke, Parkinson’s)
Residual upper limb motor impairments	Chronic liver or kidney disease
	Uncontrolled psychiatric condition
	Life expectancy<6 months
	Inability to provide informed consent (ie, severe cognitive impairment, dementia or Alzheimer’s disease)

Note: Participants with specific contraindications to transcranial magnetic stimulation, for example, epilepsy, unhealed skull fracture and increased intracranial pressure may participate in the study but will not take part in the transcranial magnetic stimulation assessment.

Once eligibility of the patient is confirmed, a clinician not involved in the research team will ask the patient whether they would be interested in hearing about a research project focusing on upper limb training. If the patient expresses an interest in hearing more about the study, a research coordinator will inform the patient of the nature of their participation and the risks and inconveniences and provide all information in oral and written form. Once the patient has given their written informed consent, they will be scheduled for their initial assessment session (see consent form in online supplemental material).

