###### Adverse events

AEs will be closely monitored at each assessment time point and during all intervention sessions using a standardised AE monitoring form. The skin at the stimulation site will be routinely checked for irritation or redness. At the start of each session, participants will be asked about any changes in their medical status since the previous visit. An AE is defined as any undesirable or unfavourable medical occurrence in a participant—such as abnormal signs, symptoms or diseases—that arises during the study, regardless of whether it is considered related to the research. AEs may include new conditions emerging after enrolment or the worsening of pre-existing conditions. Each AE will be classified according to three dimensions: (1) seriousness: serious (life-threatening, requiring or prolonging hospitalisation or causing significant disability) or non-serious (transient and mild, with no lasting consequences); (2) causality: related or unrelated to study participation and (3) expectedness: expected or unexpected.

It is possible that if skin redness occurs, a hypoallergenic moisturising cream will be applied, with an in-person follow-up at 24 hours. If redness persists, electrodes will not be placed on the same location during the next session. If an AE occurs during the intervention sessions, the interventionist and stimulation operator will jointly assess any AE to determine its severity and appropriate response. For minor events, the session will be stopped and the participant returned to their room. The SCI unit nurse will be informed to document the incident in the patient’s chart, followed by next-day follow-up before resuming training. For more severe events, an emergency code will be activated according to institutional procedures. This standardised protocol mobilises a rapid-response team of clinicians within approximately 2 min to provide immediate medical assessment and care. Subsequent discussion with the treating physician will determine when/if training can safely resume. In all cases, the principal investigator will be notified, and the event will be documented in accordance with ethics and institutional requirements. All AEs will also be recorded in the REDCap database, ensuring compliance with ethics committee reporting procedures.

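### Most of the DSMB is not independent of the trial team or host unit, and the two seriousness classes do not cover every adverse event

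*Protocol article*

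**What the plan says.** **Board.** The Data Safety and Monitoring Board section of the protocol article states: "The DSMB will comprise the head physiatrist of the SCI unit at the research centre, the research coordinators and an independent researcher", the last with expertise in clinical trials. On the board's remit it adds: "Recommendations may be based on evidence of significant adverse effects in the experimental group or on ethical considerations". The board meets yearly, or ad hoc if a safety concern arises.

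**Roles of those members elsewhere.** Project management: "The leads will report to the CIME Programme research coordinators, who meet weekly with the principal investigators". The same section says that "the project team will provide weekly updates to the SCI physiatrists". Recruitment and consent says that, once a patient has shown interest, "a research coordinator will inform the patient of the nature of their participation".

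**Event classes.** The Adverse events section classifies every event on seriousness, causality and expectedness. Seriousness takes two values: "serious (life-threatening, requiring or prolonging hospitalisation or causing significant disability) or non-serious (transient and mild, with no lasting consequences". All events go into REDCap.

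**Objective.** The first item under Secondary objectives is: "To determine the safety of the intervention (ie, minor and major adverse events (AEs".

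**The concern.** There are two separate matters here.

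The first is who sits on the board. A monitoring board is useful because people with no part in running the trial look at the safety data, by arm if needed, and can recommend changes. Here the staff to whom the trial leads report are themselves members. They would be judging a trial that they help to run. If the board looks at events by arm, that knowledge could reach people who meet the principal investigators every week. With 20 participants per arm, a by-arm listing of events may be enough for someone who knows the participants to work out individual allocations.

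The second is the seriousness rule. It reads as a complete two-way split, but the non-serious class is defined by its own narrow conditions and not as the complement of serious. Some events therefore have no class. The safety objective then uses a different pair of terms. What is at stake is the breakdown that the trial will report for its first secondary objective.

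**Working it through.** No sample size, power or error rate enters this point. The check is a reading of the stated text plus one simple proportion.

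**1. Independence of the board.**

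| Seat | What the article says of the role |
|---|---|
| Head physiatrist | Heads the SCI unit of the host centre; SCI physiatrists are updated weekly by the project team |
| Research coordinators (number not given) | Trial leads report to them; weekly meetings with the principal investigators; a coordinator gives patients the study information |
| Researcher with trial expertise | Described as independent |

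With k coordinators the board has 1 + k + 1 members, one of them described as independent. The share is 1/(2 + k). The value of k is an assumption:

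- k = 2 (the smallest reading of the plural): 1/4 = 25%
- k = 3: 1/5 = 20%
- k = 4: 1/6 = 17%

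Even if a single coordinator attended, the share would be 1/3 = 33%. On every reading the independent member is in a minority.

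**2. Access to data by arm.** The remit lets the board act on adverse effects in the experimental arm. That requires events to be separated by arm at some point. The article does not say who receives the separated data, and nothing in the section keeps it from the coordinators. The supportable statement is that they could see it.

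**3. Coverage of the seriousness classes.** Let S be the serious class (life-threatening, or hospitalisation required or prolonged, or significant disability). Let N be the non-serious class (transient, and mild, and without lasting consequences). S is a list joined by *or*; N is a list joined by *and*. An event lies outside both when it meets none of the S conditions and fails at least one N condition.

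| Event | Meets S as worded? | Meets N as worded? |
|---|---|---|
| Death | Not named | No |
| Moderate event, no hospital consequence, not life-threatening or significantly disabling | No | No (not mild) |
| Mild skin change that lasts, without significant disability | No | No (not transient) |

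The third row is not far-fetched. The Adverse events section itself foresees redness at the electrode site that persists. Depending on how long it lasts, it may not count as transient, and it is not serious on the listed criteria.

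So serious plus non-serious need not equal all events. The total stands, because every event is recorded.

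**4. Terms used for the objective.** Three vocabularies appear: minor and major (Secondary objectives), serious and non-serious (the classification), and minor and more severe (handling of events during sessions). None is mapped to another. The interventionist and the stimulation operator are also asked to judge the severity of in-session events, but severity is not one of the three classification dimensions. Under Randomisation method and blinding, the interventionist knows the allocation, so loosely defined grades leave room for judgements that differ by arm.

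**The case against.** The strongest reply is that an article condenses a fuller protocol. Open and closed sessions, and who receives unblinded data, belong in a charter. Operational definitions belong on the standardised event form. Neither is shown. That stands for the access rules, which is why the text supports only *could see*. It does not rescue the membership: a charter that excluded the coordinators would contradict what the article states. Nor does it rescue the classes, because the article states them and does not merely omit detail. A reader may take the parentheses as shorthand and assume that a death would be counted as serious. That is likely in practice, but it does not help with moderate or lasting events.

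Several stronger readings are tempting and are not supported.

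- *Allocation concealment is lost.* An independent statistician generates the sequence, with permuted blocks of 4 or 6 within 24 strata, and randomisation follows consent and the baseline assessment. Periodic review of events by arm does not in itself disclose the next assignment, and the article shows no route by which it would.
- *The trial's blinding fails.* The stated blinding covers participants and clinical assessors. The article does not say that coordinators assess outcomes or are meant to be blind. Any leak would be indirect.
- *The coordinators recruit.* Clinicians identify and refer patients, and a clinician outside the research team makes the first approach. A coordinator then informs the patient. It is also an assumption that the coordinators named in the three sections are the same people; the Project management section alone is enough to show an operating role.
- *There is no independent oversight.* One member is independent, and the ethics committee also has a role through event reporting and approval of protocol changes.
- *Adverse events are miscounted.* All are recorded, so total, causality and expectedness counts survive.

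**Conclusion.** The point holds in two limited parts, and both should be corrected.

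Most of the board is not independent of the trial team or host unit: at most 25% of members are described as independent, taking the plural as two or more coordinators. Because the remit covers adverse effects in the experimental arm, operating staff could see safety data by arm. That access is implied by the remit and not stated.

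The seriousness classes are not exhaustive and are not tied to the terms of the safety objective. The seriousness split, and the minor and major split, therefore cannot be assigned consistently for the events in the gap. The article gives no event rates, so the number affected cannot be estimated. This second part is the lighter of the two. No sample size or efficacy analysis changes.

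**What to change.** **Board.** Take the research coordinators out of DSMB membership. They may present pooled data in an open session. Restrict data by arm to members outside the study team, and say so in the section. With the coordinators removed, 1 of the 2 remaining listed members is described as independent; adding one outside member would make it 2 of 3.

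**Classification.** Name death among the serious criteria. Define non-serious as every adverse event that meets no serious criterion. Record severity as a separate item with a stated scale. Restate the safety objective in these same terms, or define minor and major through them, and align the wording used for in-session events.

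**Cost.** Edits to the board's charter, the adverse event form and a few sentences of the protocol. The downside is a smaller board, or finding one replacement member if that is wanted. Recruitment is planned from 1 September 2026, and the changes are best made before the first participant is enrolled.

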###### Adverse events

AEs will be closely monitored at each assessment time point and during all intervention sessions using a standardised AE monitoring form. The skin at the stimulation site will be routinely checked for irritation or redness. At the start of each session, participants will be asked about any changes in their medical status since the previous visit. An AE is defined as any undesirable or unfavourable medical occurrence in a participant—such as abnormal signs, symptoms or diseases—that arises during the study, regardless of whether it is considered related to the research. AEs may include new conditions emerging after enrolment or the worsening of pre-existing conditions. Each AE will be classified according to three dimensions: (1) seriousness: serious (life-threatening, requiring or prolonging hospitalisation or causing significant disability) or non-serious (transient and mild, with no lasting consequences); (2) causality: related or unrelated to study participation and (3) expectedness: expected or unexpected.

It is possible that if skin redness occurs, a hypoallergenic moisturising cream will be applied, with an in-person follow-up at 24 hours. If redness persists, electrodes will not be placed on the same location during the next session. If an AE occurs during the intervention sessions, the interventionist and stimulation operator will jointly assess any AE to determine its severity and appropriate response. For minor events, the session will be stopped and the participant returned to their room. The SCI unit nurse will be informed to document the incident in the patient’s chart, followed by next-day follow-up before resuming training. For more severe events, an emergency code will be activated according to institutional procedures. This standardised protocol mobilises a rapid-response team of clinicians within approximately 2 min to provide immediate medical assessment and care. Subsequent discussion with the treating physician will determine when/if training can safely resume. In all cases, the principal investigator will be notified, and the event will be documented in accordance with ethics and institutional requirements. All AEs will also be recorded in the REDCap database, ensuring compliance with ethics committee reporting procedures.

## Ethics and dissemination

This study was approved by the Institution Review Board (IRB) Committee en réadaptation et en déficience physique of Santé Québec Centre-Sud-de-l’Île-de-Montréal - Universitaire (MP-2024-2080) and is registered on clinicaltrial.gov. All procedures will be conducted in accordance with the principles of the Declaration of Helsinki. Any modifications to the protocol will be submitted to the IRB for approval.

Findings from this trial will be submitted for publication in peer-reviewed journals and presented at national and international conferences, such as the International Spinal Cord Society or the ASIA. A summary of the research results will be produced and distributed to all participants and clinical partners at the end of the study.
